### Intervention

Patients will receive at least one epidural injection of compound betamethasone, a corticosteroid preparation that includes 2 mg of betamethasone sodium phosphate and 5 mg of betamethasone dipropionate or dexamethasone palmitate 4 mg (contains 2.5 mg dexamethasone). The choice of compound betamethasone as a comparator in this study is based on its established efficacy and widespread use in managing inflammation and pain associated with lumbar disk herniation (Lee et al., 2022).

### Intervention description

Certified pain management physicians and orthopedic surgeons with expertise in administering epidural glucocorticoid injections will perform all procedures. The physician chose the approach (transforaminal or interlaminar) according to their usual practice. Physicians in this study were trained by the study investigators to administer the injections in a standardized manner with the use of image guidance (e.g., CT, digital subtraction angiography, or C-arm).

The injection level will be determined by MRI and the patient’s symptoms. For interlaminar injection, the level of injection will select at the spinal level of lumbar disk herniation. For the transforaminal approach, the nerve root chosen is based on prior nerve root compression identified on MRI or CT.

Patients are placed in the prone position for the procedure while a needle is inserted through the interlaminar or transforaminal route, targeting the nerve root. Upon reaching the nerve root, a sensation of nerve root paresthesia will be elicited. A contrast agent is injected alone initially to confirm the appropriate placement of the needle and ensure that the contrast reaches the epidural space.

Following this, a mixture of 0.2%–0.5% lidocaine and either DEP or betamethasone, along with the contrast agent, will be slowly injected for a total volume of 5 mL to ensure proper distribution.

For the final step, fluoroscopic imaging is performed to confirm that the injected solution properly entered the epidural space, ensuring the accuracy of the injection before the procedure is completed.

### Repeat injection

At the 4-week follow-up, patients who experience ≥50% reduction in leg pain from baseline may be considered for a repeat injection. The medication and route of administration for the repeat injection will be the same as those used in the initial treatment. Patients may also choose to receive the alternate study medication for the repeat injection. Decisions regarding repeat injections will be made collaboratively between the physician and the patient and documented in the case report form. Each patient will receive one injection initially, with a maximum of two injections allowed during the study period.

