### Primary outcome analysis

The primary outcome (NRS score at 4 weeks) will be analyzed using a linear mixed-effects model, including treatment group, time, and their interaction as fixed effects, with study center as a random effect, baseline NRS score will be adjusted as a covariate.

Non-inferiority will be assessed based on the between-group difference in mean NRS score at 4 weeks post-treatment, with a pre-specified non-inferiority margin of one point. Non-inferiority will be concluded if the upper bound of the two-sided 95% confidence interval for the between-group difference does not exceed the non-inferiority margin. Both intention-to-treat (ITT) and per-protocol (PP) analyses will be performed to ensure robustness of the results.

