### Secondary outcome analysis

The secondary outcomes of this study are leg pain scores at multiple follow-up time points, functional disability (ODI and RMDQ), mental health assessment (GAD-7 and PHQ-9), and biochemical markers. For leg pain, the NRS scores for leg pain will be analyzed at each follow-up time point using Mixed-Effects Linear Models to account for repeated measurements and intra-patient correlation. This model includes fixed effects for treatment, time, and the interaction between treatment and time. Random intercepts are used to model individual variability over time. Functional disability scores are assessed via changes in ODI and RMDQ measured at 4, 8, and 12 weeks using Mixed-Effects Linear Models. Both measures are treated as continuous variables, and the analysis accounted for repeated measurements within patients. Mental health assessments will be completed using GAD-7 and PHQ-9 anxiety and depression scores, respectively, using Mixed-Effects Linear Models at 4, 8, and 12 weeks. Serum cortisol levels at 4 weeks will be compared between treatment groups using Student’s t-test for normally distributed data, and the Mann–Whitney U test for non-normally distributed data after assessment of normality.

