### Adverse events

The occurrence of adverse events (AEs) will be reported by treatment group. A Chi-square test or Fisher’s exact test (for categorical data) will be used to compare the occurrence of AEs between the two groups.

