### Data and safety monitoring

In this trial, adverse events (AEs) and unintended effects related to the intervention or trial conduct are systematically recorded and managed following a standardized protocol. All solicited AEs are actively monitored, and participants are asked about specific symptoms immediately after the injection, at each scheduled follow-up visit, and via telephone contact during the follow-up period. Any spontaneously reported AEs are documented whenever they occur.

Trained site personnel assess the severity, causality, and duration of each event, and record these details in the case report form. Serious adverse events (SAEs), defined as any unintended medical occurrence resulting in death, being life-threatening, requiring hospitalization or prolongation of hospitalization, or resulting in persistent or significant disability/incapacity, are reported immediately to the principal investigator and the ethics committee.

All AEs, regardless of suspected causality, are included in the final analysis to ensure a comprehensive safety evaluation of dexamethasone palmitate and betamethasone in the treatment of lumbar disc herniation.

A formal independent Data and Safety Monitoring Board (DSMB) was not established in this study due to the routine clinical nature and relatively low-risk profile of epidural steroid injections. However, safety oversight is ensured through continuous monitoring by the principal investigator and periodic review by the institutional ethics committee.

Data management is performed by trained personnel at each participating center. Double data entry is used to minimize transcription errors, with two independent entries for each record. Range and consistency checks are implemented to identify outliers or data entry errors. Regular data audits are conducted to ensure completeness, accuracy, and protocol adherence.

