## Discussion

This protocol outlines a multicenter, randomized, double-blind non-inferiority trial comparing dexamethasone palmitate (DEP) with compound betamethasone for epidural injection in patients experiencing lumbar radicular pain. The study is designed to evaluate whether DEP, a novel lipophilic corticosteroid, can achieve similar clinical outcomes to a widely used particulate steroid, while potentially reducing safety concerns and improving pharmacokinetic properties.

Lumbar nerve root compression due to intervertebral disc displacement is a frequent cause of lower limb pain and functional impairment (Deyo and Mirza, 2016). Epidural steroid administration is a common interventional approach, but current evidence does not clarify the optimal choice of corticosteroid (Kreiner et al., 2014; Figueiredo et al., 2020). Particulate agents, such as betamethasone, may offer longer-lasting relief, but carry risks associated with crystal formation.

Dexamethasone palmitate (DEP) is as a prodrug of dexamethasone, consisting of dexamethasone combined with a fat emulsion that includes lecithin (Harasim-Symbor et al., 2016). Compared to dexamethasone, DEP is more readily taken up by activated macrophages due to its fat emulsion properties, which ensures robust distribution in inflammatory tissues while minimizing the risk of adverse effects (Li et al., 2024). Other benefits include a prolonged duration of action due to DEP’s liposome structure. And when mixed with local anesthetics, does not produce significant particulate formation (Hui et al., 2023).

The primary endpoint, leg pain intensity at 4 weeks post-injection, reflects both short-term and early sustained analgesic effects. Secondary endpoints include functional improvement and safety outcomes, including adverse event incidence and serum cortisol levels. A non-inferiority framework was chosen to determine whether DEP can provide outcomes that are clinically comparable to standard particulate therapy, recognizing that particulate agents may have a modest advantage in analgesic duration.

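### The repeat-injection rule requires the same drug, then lets week-4 responders choose the other one, which blurs the week-8 and week-12 drug comparison and the attribution of later adverse events

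*Protocol article*

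**What the plan says.** Under Repeat injection, the article states who is eligible at week 4: "patients who experience ≥50% reduction in leg pain from baseline may be considered for a repeat injection". It then fixes the drug: "The medication and route of administration for the repeat injection will be the same as those used in the initial treatment". The next sentence reads: "Patients may also choose to receive the alternate study medication for the repeat injection". At most two injections are allowed, and the decision is recorded in the case report form. No other section withdraws or restricts the option to change drug.

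The only margin test is at week 4. Under Primary outcome analysis: "Non-inferiority will be assessed based on the between-group difference in mean NRS score at 4 weeks post-treatment". Leg NRS, ODI, RMDQ, GAD-7 and PHQ-9 at weeks 8 and 12 are secondary outcomes. Under Secondary outcome analysis: "For leg pain, the NRS scores for leg pain will be analyzed at each follow-up time point using Mixed-Effects Linear Models". The fixed effects given for that model are treatment, time and their interaction, with no term for a repeat or a switch. The Statistical analyses section names intention-to-treat and per-protocol analyses without placing switchers in either.

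For safety, the Adverse events section says: "The occurrence of adverse events (AEs) will be reported by treatment group". Table 1 shows collection at every visit to week 12, and Data and safety monitoring agrees: "participants are asked about specific symptoms immediately after the injection, at each scheduled follow-up visit, and via telephone contact during the follow-up period".

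**The concern.** The two sentences on the repeat drug give different instructions, so two centres could act in opposite ways and both claim to comply. The permissive sentence matters more. It lets patients selected by their response move to the comparator drug by choice, after which they are still analysed under a treatment label that no longer describes what they received.

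This falls on the visits that bear most on the trial's own reasoning. The Discussion justifies the non-inferiority framework by "recognizing that particulate agents may have a modest advantage in analgesic duration". After week 4, a difference in duration could show only at weeks 8 and 12. If the second drug drives outcomes at those visits, switching pulls the arms together and the drugs look more alike than they are. In a non-inferiority trial that is the unsafe direction for supportive evidence.

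Safety is a stated reason for interest in dexamethasone palmitate. If events are tabulated by assigned arm, one that follows a second injection with the other drug is charged to the first. The article already bars other invasive procedures because they could influence outcomes (Strategies to improve adherence to interventions). An injection of the comparator is at least as direct an influence on this comparison.

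**Working it through.** **Inputs from the article (Study sample size).** SD 2.2, margin 1 point, true difference 0 at week 4, one-sided α 0.025, power 0.90, 1:1 allocation, 10% loss.

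**The plan's own figure.** n per arm = 2 × (1.960 + 1.282)² × 2.2² / 1² ≈ 101.7, rounded up to 102. With 10% loss, 102 / 0.9 = 113.3, rounded up to 114. Both match the article. This calculation concerns week 4 and is not in question.

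**Assumptions, because the article gives no figures.**
- A share c of an arm switches, with c = 5–10% (about 5–10 of 102 patients).
- The true drug difference at week 8 or 12 is 1.0 point.
- The week-4 SD of 2.2 and 102 per arm also apply at those visits.
- The comparison is a simple two-sample one, two-sided 5%, used as a stand-in for the planned mixed model.

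**Dilution.** If a share c of each arm takes the other drug and its full effect transfers, each arm mean moves a fraction c of the way towards the other. The observed difference is then 1 − 2c. In general it is 1 − k·c:
- k = 2: both arms switch, full effect transfers.
- k = 1: one arm switches with full effect, or both arms switch with half the effect.
- k = 0.5: one arm switches, half the effect transfers.

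**Power.** SE = 2.2 × √(2/102) = 0.308, and power = Φ(d/0.308 − 1.96).

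| Case | d at c = 5% | Power | d at c = 10% | Power |
|---|---|---|---|---|
| No switching | 1.00 | 90.1% | 1.00 | 90.1% |
| k = 0.5 | 0.975 | 88.6% | 0.95 | 86.9% |
| k = 1 | 0.95 | 86.9% | 0.90 | 83.2% |
| k = 2 | 0.90 | 83.2% | 0.80 | 73.8% |

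**How wide the range could be.** Suppose 40–60% respond, 30–100% of responders have a repeat, and 10–50% of those switch. Then c runs from 0.4 × 0.3 × 0.1 = 1.2% to 0.6 × 1 × 0.5 = 30% of each arm. With k = 2 the difference kept runs from 97.6% to 40%, and power from 88.7% to 25.4%. With k = 1 the difference kept runs from 98.8% to 70%. So 5–10% lies well inside what the rule would allow, but a rate near zero is also possible.

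**Cost of a sensitivity analysis that sets post-switch scores aside.** If those scores contribute nothing, SE = 0.308/√0.95 = 0.316 to 0.308/√0.90 = 0.325, an interval 2.6–5.4% wider.

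**The case against.** The strongest reply is that the wording of the second sentence marks an exception to a same-drug default, so there is a deliberate design choice and no contradiction. That reading is fair, but it leaves the switch in place, and the switch is what does the harm.

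The size is also open to challenge. Only patients who did well on their first drug qualify, and the article gives no reason why many of them would change. It states no expected difference at weeks 8 or 12, and if there is none, there is nothing to dilute. The 74% figure needs 10% switching in both arms with the second drug alone determining later pain. All of this stands: the figures illustrate a possible effect and do not estimate it.

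It is also true that the week-4 conclusion and sample size are untouched, that no margin test is planned at weeks 8 or 12, and that the as-randomised comparison remains valid for starting strategies. These points limit the seriousness of the concern without removing it.

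How switchers are analysed, and whether the safety group means drug assigned or drug received, could properly sit in an analysis plan that is not shown. The case report form should hold what is needed to tabulate events either way, so misattribution is possible but not certain. However, no analysis plan can undo switches that the protocol allows.

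Finally, same-drug repeats would still obscure how long a single injection lasts. That is a separate limitation. Removing the switch would at least mean that the arms differ only in the study drug given.

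**Conclusion.** The concern holds and should be fixed. The article gives conflicting instructions on the repeat drug and, on either reading, authorises a non-randomised, responder-only crossover at week 4. The primary non-inferiority test is not affected, provided leg pain is scored before any repeat. From week 8 onward the by-arm results describe starting strategies rather than drugs, and adverse-event attribution becomes uncertain for anyone who switched.

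The wording and its consequence for interpretation are certain; the numerical size is not. At an assumed 5–10% switching, a true 1.0-point difference would shrink to between 0.975 and 0.80, and power would fall from 90% to between 89% and 74%. The result depends on which arms switch and how much of the second drug's effect carries through.

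**What to change.** Delete the sentence that allows the alternate drug, so that any repeat uses the blinded assigned drug by the original route. Add a sentence stating that the week-4 NRS is scored before a repeat injection is given. This costs no data and leaves 102 evaluable and 114 randomised per arm unchanged. Patients lose the option to switch.

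If the sponsor wishes to keep switching:

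1. Keep the as-randomised analysis at weeks 8 and 12, and label it a comparison of starting strategies.
2. Add a sensitivity analysis that sets aside post-switch scores and imputes them conditional on arm, baseline and week-4 response. Week-4 response is needed because every switcher is a responder. The interval would be about 3–5% wider at 5–10% switching.
3. Report adverse events by drug received, separately before and after the repeat injection, which needs one extra table.

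As an editorial matter, the Study design section lists safety assessment at day 1 and week 4 only. It should be brought into line with Table 1.

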### Criteria for trial discontinuation

Participation in the trial may be discontinued under the following conditions:Occurrence of any serious adverse event related to the study intervention;Significant worsening of symptoms, including increased pain intensity or new or progressive neurological deficits (e.g., motor weakness, sensory loss);Development of procedure-related complications (e.g., infection, bleeding, or suspected vascular injury);Any unexpected clinical condition that, in the judgment of the primary investigator, makes continued participation unsafe;Withdrawal of consent by the participant at any time.

All discontinuation events will be documented, including the reason and timing, to ensure transparency in data analysis.

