**Methods:**

This multicenter, randomized, double-blind, non-inferiority trial will enroll 228 patients with confirmed lumbar disc herniation and radicular pain. Participants will be randomly assigned (1:1) to receive an image-guided epidural injection of either DEP or compound betamethasone via interlaminar or transforaminal approach. Follow-up assessments will occur at 1 day, 1 week, 2 weeks, 4 weeks, 8 weeks, and 12 weeks post-injection. The primary outcome is leg pain intensity at 4 weeks, measured by the numeric rating scale (NRS). Secondary outcomes include NRS at other time points, functional disability (ODI and RMDQ), mental health (GAD-7 and PHQ-9), morning serum cortisol, patient satisfaction, and adverse events. A second injection may be administered at 4 weeks based on clinical response.

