### Interpreting instances of missing data

For missing data, we will apply multiple imputation methods to generate plausible values for missing observations under the assumption that data is missing at random. Sensitivity analyses are conducted to assess the impact of missing data by comparing results using different methods for handling missing data (e.g., Last Observation Carried Forward and multiple imputation). All statistical analyses are conducted using SPSS (version 25.0 or higher) or R software. Interim analyses will be used to recalculate the sample size.

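### Patients may leave the trial for increased pain before the week-4 score, and no named missing-data method is designed to test whether this favours non-inferiority

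*Protocol article*

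**What the plan says.** The section on criteria for trial discontinuation opens with "Participation in the trial may be discontinued under the following conditions" and lists among the grounds "Significant worsening of symptoms, including increased pain intensity or new or progressive neurological deficits". What may end is participation in the trial, not only treatment, and the ground is not tied to any visit or period. On what follows, the section says only: "All discontinuation events will be documented, including the reason and timing, to ensure transparency in data analysis". It does not say whether later outcome scores are still sought.

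The primary outcome is leg NRS at 4 weeks. Before that, pain is scored at day 1, week 1 and week 2 (Table 1), so no score is scheduled between weeks 2 and 4. Each patient receives one injection initially, and a repeat is considered only at the 4-week visit (Repeat injection).

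For missing data the article states: "we will apply multiple imputation methods to generate plausible values for missing observations under the assumption that data is missing at random". The sensitivity analysis compares methods, described as "e.g., Last Observation Carried Forward and multiple imputation". The primary analysis section adds: "Both intention-to-treat (ITT) and per-protocol (PP) analyses will be performed to ensure robustness of the results".

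**The concern.** Between the injection and week 4 there is no further study treatment to stop. A discontinuation for increased pain in that window can therefore act only on follow-up. Read as written, it can remove the week-4 scores of patients doing badly, for a reason that is the outcome itself.

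Imputation under missing at random then fills the gap from patients with a similar recorded history who stayed. If the worsening was never recorded, that history looks better than the patient's true state and the imputed score is too low. LOCF carries forward a score from before the worsening and can err in the same direction.

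In a superiority trial, a shrunken difference usually works against the claim. Here it works for the claim. If more patients leave for worsening on DEP than on betamethasone, the upper confidence limit moves down and a false conclusion of non-inferiority becomes more likely. Neither an intention-to-treat nor a per-protocol analysis restores a week-4 score that was not collected.

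**Working it through.** **Inputs from the article (Study sample size; Primary outcome analysis).** SD 2.2, margin 1, one-sided alpha 0.025, power 0.90, assumed true difference 0, 102 evaluable and 114 randomised per group, 10% loss. Non-inferiority is concluded if the upper 95% limit does not exceed 1.

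**1. The plan's own figure.** n = 2 × 2.2² × (1.960 + 1.282)² / 1² = 9.68 × 10.51 = 101.7, so 102 per group. Then 102 / 0.90 = 113.3, so 114. Both figures are reproduced.

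**2. What a shift does to the error rate.** SE = 2.2 × √(2/102) = 0.308. If the true difference equals the margin and the estimate is shifted by b towards zero, P(false non-inferiority) = Φ(b/SE − 1.96). With b = 0 this is 2.5%.

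**3. How large b could be.** To a first approximation b = (w_DEP − w_BET) × D. Here w is the share withdrawn for worsening in each arm, and D is how far the filled-in score lies below the true one. The article gives neither quantity, so every value below is an assumption.

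*Scenario A, fluctuating pain with unrecorded worsening.* 114 per arm; baseline mean 6.5 (SD 1.5); week-4 control mean 3.0 (SD 2.2); serial correlation 0.8; scores kept within 0 to 10. A patient withdraws with probability 0.8 if unrecorded week-3 or week-4 pain is at least one point above baseline.
- Withdrawn: 2.8% on betamethasone, 7.5% on DEP.
- Estimated difference: 0.994 with full follow-up, 0.905 after imputation under missing at random. Shift 0.089.
- False non-inferiority: Φ(−1.96 + 0.089/0.308) = Φ(−1.67) = 4.7%. For a shift of 0.10, Φ(−1.635) = 5.1%.

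*Scenario B, a sudden, lasting 3-point worsening after week 2 with no score recorded.* 114 per arm, correlation between visits 0.6, 4,000 runs, true difference 1, average withdrawal held at 10%. The formula in step 2 is shown beside the simulation.

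| Withdrawn, DEP / betamethasone | b = difference × 3 | Formula | Simulated, imputation | Simulated, LOCF |
|---|---|---|---|---|
| 10% / 10% | 0 | 2.5% | 2.6% | 2.5% |
| 12% / 8% | 0.12 | 5.8% | 6.1% | 6.3% |
| 13% / 7% | 0.18 | 8.4% | 8.4% | 8.9% |
| 15% / 5% | 0.30 | 16.2% | 16.8% | 18.1% |

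At 12% / 8%, the formula gives 3.4% for D = 1 and 4.5% for D = 2. Scenario B assigns the whole 10% loss allowance to worsening, so its lower rows are upper-range illustrations.

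**4. When the effect disappears.** If the worsened score is recorded at a visit before withdrawal (simulated, 12.8% withdrawn on DEP and 5.6% on betamethasone), imputation gives 0.997 against 0.999 with full data, and false non-inferiority is 3.0%. LOCF then errs the other way, at 1.135 and 0.8%. With equal withdrawal the shift is nil (first row of the table).

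**5. Would comparing imputation with LOCF reveal it?** It depends on the pattern. In scenario A, LOCF gave 0.97 to 0.98, close to the full-data 0.994 and visibly different from the imputed 0.905. In scenario B at 15% / 5%, both methods gave 0.695 against a true 1.0, so the comparison would show nothing.

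**The case against.** Several points on the other side are fair.

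- *A reader might infer that the plan never tests for this.* The documents do not support that. The sensitivity list is introduced as examples, a separate analysis plan may add to it, and in scenario A the planned comparison with LOCF would have shown the gap. What stands is that no named method is designed for withdrawal because of worsening, and whether LOCF exposes it is a matter of chance.
- *A reader might infer that bias is certain.* It is not. It needs more withdrawals on DEP and worsening that escapes the recorded scores. Pain is scored three times before week 4, symptoms are asked about at visits and by telephone, discontinuation is permissive, and oral rescue medication is allowed. These points lower the likely rates. On the other hand, unequal withdrawal is no extra assumption where the test must protect: with DEP worse by the margin, one threshold common to both arms gave 12.8% against 5.6%.
- *Larger figures follow if unchanged pain counts as worsening.* The text requires significant worsening, so such figures do not apply.
- *A reader might infer that the per-protocol set drops these patients, or that requiring both analysis sets would cure the problem.* The article does not define the per-protocol set, and requiring both sets would not restore scores that were not collected.
- *An article may leave missing-data detail to a fuller document.* That is true of further sensitivity analyses. But the outcome-linked discontinuation ground and the missing-at-random assumption are both stated here, and no later analysis plan can recover a score that was never collected.

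**Conclusion.** The point holds in conditional form. The article lets participation end for the construct of its primary outcome and does not say that the week-4 score is still collected. It then imputes under missing at random with no named analysis aimed at this mechanism. On the assumptions closest to the text (about 3% against 7.5% withdrawn, worsening unrecorded), the estimate shifts by about 0.09 to 0.10 of the 1-point margin and false non-inferiority roughly doubles, from 2.5% to about 5%. With sudden, lasting worsening it is about 6% at 12% against 8% withdrawn, and higher with greater imbalance. It is near nil with equal withdrawal or, under missing at random, when the worsened score is recorded before exit. The withdrawal rates and the size of worsening are assumptions; the SE and the margin come from the article. The sample size is not affected. No view is taken on the clinical discontinuation criteria themselves.

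**What to change.** 1. Leave the discontinuation criteria unchanged, and state that meeting one does not end outcome collection. Record a leg NRS at the time of discontinuation. Obtain the week-4 leg NRS, by telephone if needed, from every randomised patient who has not withdrawn consent. Telephone contact is already part of safety follow-up.
2. Alongside the planned methods, add a delta-adjusted (tipping-point) multiple imputation: add increasing penalties to the imputed DEP scores and report the penalty at which non-inferiority is lost.

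The cost is a few sentences, some telephone calls and one extra analysis. The downside is that the result may look slightly less favourable to DEP. The first item matters only while week-4 scores can still be collected, so it should come first.
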